### Summary of known and potential risks and benefits

Adverse reactions to HEPSERA identified from placebo-controlled and open label studies include the following: asthenia, headache, abdominal pain, diarrhea, nausea, dyspepsia, flatulence, increased creatinine, and hypophosphatemia.

Adefovir dipivoxil 10 mg/day is generally well tolerated in patients with chronic HBV infection; there were no marked increases in adverse events or laboratory abnormalities compared with placebo in a pooled analysis of 48-week data from two double-blind trials. Asthenia and diarrhoea occurred more frequently than with placebo in one of the placebo-controlled studies, while headache and abdominal pain occurred more frequently in the other study. Within 48 weeks 2% of patients from one study and no patients in the other study discontinued treatment because of adverse events.

Nephrotoxicity characterized by a delayed onset of gradual increases in serum creatinine and decreases in serum phosphorus was historically shown to be the treatment-limiting toxicity of adefovir dipivoxil therapy at substantially higher doses in HIV-infected patients (60 and 120 mg daily) and in chronic hepatitis B patients (30 mg daily). Chronic administration of HEPSERA (10 mg once daily) may result in delayed nephrotoxicity. The overall risk of nephrotoxicity in patients with adequate renal function is low. However, this is of special importance in patients at risk of or having underlying renal dysfunction and patients taking concomitant nephrotoxic agents such as cyclosporine, tacrolimus, aminoglycosides, vancomycin and non-steroidal anti-inflammatory drugs. It is important to monitor renal function for all patients during treatment with HEPSERA, particularly for those with pre-existing or other risks for renal impairment. Patients with renal insufficiency at baseline or during treatment may require dose adjustment. The risks and benefits of HEPSERA treatment should be carefully evaluated prior to discontinuing HEPSERA in a patient with treatment-emergent nephrotoxicity.

Severe acute exacerbation of hepatitis has been reported in patients who have discontinued anti-hepatitis B therapy, including therapy with HEPSERA. Hepatic function should be monitored at repeated intervals with both clinical and laboratory follow-up for at least several months in patients who discontinue HEPSERA. If appropriate, resumption of anti-hepatitis B therapy may be warranted.

In clinical trials of HEPSERA, exacerbations of hepatitis (ALT elevations 10 times the upper limit of normal or greater) occurred in up to 25% of patients after discontinuation of

HEPSERA. These events were identified in studies GS-98-437 and GS-98-438 (N=492). Most of these events occurred within 12 weeks of drug discontinuation. These exacerbations generally occurred in the absence of HBeAg seroconversion, and presented as serum ALT elevations in addition to re-emergence of viral replication. In the HBeAg-positive and HBeAg-negative studies in patients with compensated liver function, the exacerbations were not generally accompanied by hepatic decompensation. However, patients with advanced liver disease or cirrhosis may be at higher risk for hepatic decompensation. Although most events appear to have been self-limited or resolved with re-initiation of treatment, severe hepatitis exacerbations, including fatalities, have been reported. Therefore, patients should be closely monitored after stopping treatment.

Prior to initiating HEPSEARA therapy, HIV antibody testing should be offered to all patients. Treatment with anti-hepatitis B therapies, such as HEPSEARA, that have activity against HIV in a chronic hepatitis B patient with unrecognized or untreated HIV infection may result in emergence of HIV resistance. HEPSEARA has not been shown to suppress HIV RNA in patients; however, there are limited data on the use of HEPSEARA to treat patients with chronic hepatitis B co-infected with HIV.

Lactic acidosis and severe hepatomegaly with steatosis, including fatal cases, have been reported with the use of nucleoside analogs alone or in combination with antiretrovirals.

A majority of these cases have been in women. Obesity and prolonged nucleoside exposure may be risk factors. Particular caution should be exercised when administering nucleoside analogs to any patient with known risk factors for liver disease; however, cases have also been reported in patients with no known risk factors. Treatment with HEPSEARA should be suspended in any patient who develops clinical or laboratory findings suggestive of lactic acidosis or pronounced hepatotoxicity (which may include hepatomegaly and steatosis even in the absence of marked transaminase elevations).

#### Description and justification of route of administration, dosages, dosage modifications and method of administration

The recommended dose of HEPSEARA in chronic hepatitis B patients for patients  $\geq 12$  years of age with adequate renal function is 10 mg, once daily, taken orally, without regard to food. The optimal duration of treatment is unknown (42).

Adefovir dipivoxil is absorbed rapidly following oral administration. The drug is cleaved to adefovir which, in turn, is phosphorylated intracellularly to adefovir diphosphate (the active moiety). Following a single dose of adefovir dipivoxil, the bioavailability of adefovir was 59%.

Adefovir is excreted renally as unchanged drug (steady-state renal clearance [ $CL_R$ ] 154 mL/h/kg). The median steady-state terminal elimination half-life was  $\approx 7$  hours in 14 patients with chronic hepatitis B. In patients with moderate to severe renal dysfunction, the systemic exposure of adefovir increased and the  $CL_R$  decreased.

In healthy volunteers, there were no clinically relevant drug interactions when lamivudine, paracetamol (acetaminophen), ibuprofen or cotrimoxazole (trimethoprim/sulfamethoxazole) were coadministered with adefovir dipivoxil.

Significantly increased drug exposures were seen when HEPSERA was administered to adult patients with renal impairment. Therefore, the dosing interval of HEPSERA should be adjusted in adult patients with baseline creatinine clearance  $<50$  mL/min using the following suggested guidelines (see Table 4). The safety and effectiveness of these dosing interval adjustment guidelines have not been clinically evaluated. Renal function should be monitored in all patients; patients receiving concomitant drugs that are excreted renally or known to affect renal function should be closely monitored (43). Additionally, it is important to note that these guidelines were derived from data in patients with pre-existing renal impairment at baseline. They may not be appropriate for patients in whom renal insufficiency evolves during treatment with HEPSERA. Therefore, clinical response to treatment and renal function should be closely monitored in these patients. (42). Patients who discontinue adefovir dipivoxil should be closely monitored for exacerbation of hepatitis (43).

|                                      | Creatinine Clearance (mL/min)Creatinine clearance calculated by Cockcroft-Gault method using lean or ideal body weight. |                      |                      |                                       |
|--------------------------------------|-------------------------------------------------------------------------------------------------------------------------|----------------------|----------------------|---------------------------------------|
|                                      | $\geq 50$                                                                                                               | 30–49                | 10–29                | Hemodialysis Patients                 |
| Recommended dose and dosing interval | 10 mg every 24 hours                                                                                                    | 10 mg every 48 hours | 10 mg every 72 hours | 10 mg every 7 days following dialysis |

Table 4.

The pharmacokinetics of adefovir have not been evaluated in non-hemodialysis patients with creatinine clearance <10 mL/min; therefore, no dosing recommendation is available for these patients.

No clinical data are available to make dosing recommendations in adolescent patients with renal insufficiency

### **Tenofovir disoproxil fumarate (Viread®)**

#### Summary of findings from non-clinical and clinical studies

Tenofovir disoproxil fumarate (VIREAD®), the oral prodrug of tenofovir, is a nucleotide analog reverse transcriptase inhibitor with activity against HIV and HBV. (G. alvarez-uria, british hiv association 2009) For this reason it has been widely used in HIV-infected patients with HBV coinfection.

The pharmacological action is exerted through inhibiting viral polymerase- reverse transcriptase by direct binding, and after incorporation into DNA, by termination of the DNA chain due to the absence of a requisite 3'hydroxyl on the tenofovir molecule.

Functioning of the enzyme polymerase (reverse transcriptase) is necessary for the replication of HIV and HBV by producing viral DNA. It remains active against lamivudine-resistant HBV, and it has known activity against HBV both in patients with HBV mono-infection and in patients with HIV-1 and HBV coinfection.

Tenofovir is structurally similar to adefovir. In vitro studies showed that tenofovir and adefovir are equipotent. Because tenofovir appears to be less nephrotoxic, the approved dose is much higher than that of adefovir, 300mg vs 10mg daily. This may explain why tenofovir has more potent antiviral activity in clinical studies. Tenofovir is generally well tolerated but it has been rarely reported to cause Fanconi syndrome and renal insufficiency (44).

Tenofovir DF, is currently approved in the United States and more than 50 other countries for the treatment of human immunodeficiency virus type 1 (HIV-1), and it was recently approved for the treatment of chronic HBV infection in the United States, Canada, Europe, Australia and Turkey.

Recently two phase 3 studies were performed to compare the safety and efficacy of tenofovir DF with adefovir dipivoxil in HBeAg-negative or HBeAg positive patients (32). In these studies among patients with chronic HBV infection, tenofovir DF at a daily dose of 300mg

had superior antiviral efficacy with a similar safety profile as compared with adefovir dipivoxil at a daily dose of 10mg through week 48. The primary endpoint of both HBV DNA level of less than 400 copies/ml and histologic improvement was reached in 71% vs. 49% among HBeAg negative patients and 67% vs. 12% among HBeAg positive patients.

Another recent long-term follow-up study of 34 months showed that tenofovir DF was able to control HBV replication in most HIV-coinfected patients, regardless of previous lamivudine treatment. A sustained virologic response rate of HBV DNA was achieved in 83%.

#### Summary of known and potential risks and benefits

Lactic acidosis and severe hepatomegaly with steatosis, including fatal cases, have been reported with the use of nucleoside analogs, including VIREAD, in combination with other antiretrovirals. A majority of these cases have been in women. Obesity and prolonged nucleoside exposure may be risk factors. Particular caution should be exercised when administering nucleoside analogs to any patient with known risk factors for liver disease; however, cases have also been reported in patients with no known risk factors. Treatment with VIREAD should be suspended in any patient who develops clinical or laboratory findings suggestive of lactic acidosis or pronounced hepatotoxicity (which may include hepatomegaly and steatosis even in the absence of marked transaminase elevations).

Discontinuation of anti-HBV therapy, including VIREAD, may be associated with severe acute exacerbations of hepatitis. Patients infected with HBV who discontinue VIREAD should be closely monitored with both clinical and laboratory follow-up for at least several months after stopping treatment. If appropriate, resumption of anti-hepatitis B therapy may be warranted.

Tenofovir is principally eliminated by the kidney. Renal impairment, including cases of acute renal failure and Fanconi syndrome (renal tubular injury with severe hypophosphatemia), has been reported with the use of VIREAD.

It is recommended that creatinine clearance be calculated in all patients prior to initiating therapy and as clinically appropriate during therapy with VIREAD. Routine monitoring of calculated creatinine clearance and serum phosphorus should be performed in patients at risk for renal impairment.

Dosing interval adjustment of VIREAD and close monitoring of renal function are recommended in all patients with creatinine clearance <50 mL/min.

No safety or efficacy data are available in patients with renal

impairment who received VIREAD using these dosing guidelines, so the potential benefit of VIREAD therapy should be assessed against the potential risk of renal toxicity. VIREAD should be avoided with concurrent or recent use of a nephrotoxic agent.

#### Description and justification of route of administration and dosage

Dosages, dosage modifications and method of administration

For the treatment of HIV-1 or chronic hepatitis B: The dose of VIREAD is 300 mg once daily taken orally, without regard to food.

In the treatment of chronic hepatitis B, the optimal duration of treatment is unknown.

Significantly increased drug exposures occurred when VIREAD was administered to patients with moderate to severe renal impairment.

Therefore, the dosing interval of VIREAD should be adjusted in patients with baseline creatinine clearance <50 mL/min. Dosing interval needs to be adjusted to every 48 hours or every 72 to 96 hours in patients with a creatinine clearance of 30-49 or 10-29 mL/min respectively. In hemodialysis patients dose should be given every 7 days or after a total of approximately 12 hours of dialysis. (Generally once weekly assuming three hemodialysis sessions a week of approximately 4 hours duration).

These dosing interval recommendations are based on modeling of single-dose pharmacokinetic data in non-HIV and non-HBV infected subjects with varying degrees of renal impairment, including end-stage renal disease requiring hemodialysis. The safety and effectiveness of these dosing interval adjustment recommendations have not been clinically evaluated in patients with moderate or severe renal impairment, therefore clinical response to treatment and renal function should be closely monitored in these patients

No dose adjustment is necessary for patients with mild renal impairment (creatinine clearance 50–80 mL/min). Routine monitoring of calculated creatinine clearance and serum phosphorus should be performed in patients with mild renal impairment

The pharmacokinetics of tenofovir have not been evaluated in non-hemodialysis patients with creatinine clearance <10 mL/min; therefore, no dosing recommendation is available for these patients.

VIREAD is available as tablets. Each tablet contains 300 mg of tenofovir disoproxil fumarate, which is equivalent to 245 mg of tenofovir disoproxil. The tablets are almondshaped, light blue, film-coated, and debossed with “GILEAD” and “4331” on one side

and with “300” on the other side (45).

No preparation and labelling of Investigational Medicinal Products is applicable to all of the investigational products.

#### Drug accountability

The investigator or the hospital pharmacist must maintain an adequate record of the receipt of all trial supplies. Dispensation and return, or if applicable, destruction, of the study medication must be documented by using the appropriate forms. All these records must be available for inspection at any time.

During the trial compliance will be assessed by counting returned dosage units. Subject will also be asked to record their drug intake in a diary.

## **7. METHODS**

### **7.1 Study parameters/endpoints**

#### **7.1.1. Main study parameter/endpoint**

The primary objective is to demonstrate the superior efficacy of combination therapy (Peg-IFN and adefovir or Peg-IFN and tenofovir) in loss of HBsAg compared to no treatment in subjects with chronic HBV and low viral loads.

HBsAg loss is defined as HBsAg level < 0.05 IU/mL.

#### **7.1.2. Secondary study parameters/endpoints**

The secondary objectives are to evaluate:

- a. the rate of HBsAg loss and anti-HBs serconversion,
- b. To establish predictive markers for response at baseline and during the first 12 weeks of treatment. ( see paragraph 2. objectives)

#### **7.1.3. Other study parameters**

Baseline characteristics will be documented of all patients. Age, weight, sex, medical history, cause of infection, interferon naïve, previous treatment, histology activity index, ISHAK fibrosis score, prescence of cirrhosis, ethnicity will be documented.

### **7.2. Randomisation, blinding and treatment allocation**

Patients will be randomized unblinded to one of the 3 groups. A stratification for hepatitis B genotype A will be performed.

### **7.3. Study procedures**

Study procedures are listed in table 2.

### **7.4. Withdrawal of individual subjects**

Subjects can leave the study at any time for any reason if they wish to do so without any consequences. The investigator can decide to withdraw a subject from the study for urgent medical reasons.

#### **7.4.1. Specific criteria for withdrawal**

Subjects may be withdrawn from the treatment if:

1. a serious side effect occurs.

2. they fail to comply with the protocol requirements or to cooperate with the investigator.

Subjects must discontinue all study medication or have their treatment modified for the following reasons:

1. all study medication must be discontinued and a subject must be withdrawn from the trial if he/she withdraws informed consent.
2. all study medication must be discontinued if a subject has a positive pregnancy test, or if the subject/partner is non-compliant with contraception requirements.

#### **7.5. Replacement of individual subjects after withdrawal**

After withdrawal of an individual subjects no replacement will take place, 10% drop out is calculated in the power of this study.

#### **7.6. Follow-up of subjects withdrawn from treatment**

Follow up of subject withdrawn from treatment will be done according the EASL HBV guidelines.

#### **7.7. Premature termination of the study**

The study will be terminated prematurely in case of serious adverse events.

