#### Summary of known and potential risks and benefits

PEGASYS can cause a broad variety of serious adverse reactions . The most common life-threatening or fatal events induced or aggravated by PEGASYS were depression, suicide, relapse of drug abuse/overdose, and bacterial infections, each occurring at a frequency of  $< 1\%$ . Hepatic decompensation occurred in 2% (10/574) of CHC/HIV patients .

In clinical trials of 48 week treatment duration, the adverse event profile of PEGASYS® in chronic hepatitis B was similar to that seen in chronic hepatitis C PEGASYS® monotherapy

use, except for exacerbations of hepatitis. Six percent of PEGASYS® treated patients in the hepatitis B studies experienced one or more serious adverse events.

The most common or important serious adverse events in the hepatitis B studies were infections (sepsis, appendicitis, tuberculosis, influenza), hepatitis B flares, anaphylactic shock, thrombotic thrombocytopenic purpura.

The most commonly observed adverse reactions were pyrexia (54% vs. 4%), headache (27% vs. 9%), fatigue (24% vs. 10%), myalgia (26% vs. 4%), alopecia (18% vs. 2%), and anorexia (16% vs. 3%) in the PEGASYS and lamivudine groups respectively.

Overall 5% of hepatitis B patients discontinued PEGASYS therapy and 40% of patients required modification of PEGASYS dose. The most common reason for dose modification in patients receiving PEGASYS therapy was for laboratory abnormalities including neutropenia (20%), thrombocytopenia (13%), and ALT disorders (11%).

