### **8.2 Section 10 WMO event**

In accordance to section 10, subsection 1, of the WMO, the investigator will inform the subjects and the reviewing accredited METC if anything occurs, on the basis of which it appears that the disadvantages of participation may be significantly greater than was foreseen in the research proposal. The study will be suspended pending further review by the accredited METC, except insofar as suspension would jeopardise the subjects' health. The investigator will take care that all subjects are kept informed.

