### **8.3. Adverse and serious adverse events**

Adverse events are defined as any undesirable experience occurring to a subject during a clinical trial, whether or not considered related to the investigational drug.

A serious adverse event is any untoward medical occurrence or effect that at any dose results in death;

- is life threatening (at the time of the event);
- requires hospitalisation or prolongation of existing inpatients' hospitalisation;
- results in persistent or significant disability or incapacity;
- is a congenital anomaly or birth defect;

- is a new event of the trial likely to affect the safety of the subjects, such as an unexpected outcome of an adverse reaction, lack of efficacy of an IMP used for the treatment of a life threatening disease, major safety finding from a newly completed animal study, etc.

Medical and scientific judgment should be exercised in deciding whether expedited reporting is appropriate in other situations, such as important medical events that may not be immediately life-threatening or result in death or hospitalization but may jeopardize the patient or may require intervention to prevent one of the outcomes listed in the definitions above. These situations should also usually be considered serious.

The term severe is a measure of intensity, thus a severe adverse event is not necessarily serious. For example, nausea of several hours' duration may be rated as severe, but may not be clinically serious.

A death occurring during the study or which comes to the attention of the investigator within 4 weeks after stopping the treatment or during the 24 weeks of protocol-defined follow-up period, whether considered treatment-related or not, must be reported.

Any pregnancy which occurs during a clinical study with an investigational drug must be reported as an SAE for tracking purposes. All pregnancies which are identified during this study need to be followed to conclusion and outcome reported.

Female patients should immediately inform the Investigator of any pregnancies and should be instructed by the Investigator to stop taking study medication. (Pregnancies occurring up to 3 months after the completion of the study must also be reported to the Investigator). The Investigator should counsel the patient, discuss the risks of continuing with the pregnancy and the possible effects on the fetus. Monitoring of the patient should continue until the conclusion of the pregnancy.

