## **9.2 .Interim analysis**

After inclusion of 50,100 and 150 patients and yearly during longterm follow-up an interim analysis will be performed by the investigator. The statistical test is the two-sided Fisher's exact test. Stopping rules for the study are the occurrence of serious adverse events.

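### Sections 7.7 and 9.2 make the bare occurrence of serious adverse events the rule for ending the study, although section 6.2 leads one to expect such events and other sections assume the trial carries on after them

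*Protocol*

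**What the plan says.** **The rule.** Section 7.7 reads in full: "The study will be terminated prematurely in case of serious adverse events". Section 9.2, after listing interim analyses at 50, 100 and 150 inclusions and yearly in long-term follow-up, adds: "Stopping rules for the study are the occurrence of serious adverse events". Neither section gives a count, a rate, a causality or expectedness condition, or a comparison between arms.

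**How wide the trigger is.** Section 8.3 defines adverse events "whether or not considered related to the investigational drug", and its definition of an SAE adds no relatedness condition. Any hospitalisation qualifies. A pregnancy is also to be reported as an SAE, for tracking.

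**What is foreseen.** Section 6.2, in the Peg-IFN risk summary, says that six percent of Peg-IFN "treated patients in the hepatitis B studies experienced one or more serious adverse events". Those were trials of 48 weeks of treatment, the duration used here.

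**What happens after an SAE elsewhere in the protocol.**
- Section 7.4.1 leaves individual withdrawal after a serious side effect to discretion ("Subjects may be withdrawn from the treatment if").
- Section 8.3.1 asks for half-yearly listings of SUSARs not reported expedited.
- Section 8.3.2 asks for yearly aggregated tables of serious adverse reactions for as long as the trial runs.
- Section 11.3 puts SAEs in each annual progress report.

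**The statutory route.** Section 8.2 applies when it appears that "the disadvantages of participation may be significantly greater than was foreseen in the research proposal". Its consequence is: "The study will be suspended pending further review by the accredited METC".

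**The concern.** A stopping rule should separate a trial that is going as foreseen from one that is not. This one cannot. Its only condition is that SAEs occur, and the protocol itself expects them in patients given Peg-IFN. An unrelated hospital admission satisfies the wording as well as a drug-induced death does.

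Two outcomes are possible, and both are bad. If the rule is followed, the trial may end on events that were accepted when it was approved, before its primary question is answered. If it is not followed, each foreseen SAE is a departure from sections 7.7 and 9.2, and the real decision to continue or stop has no written criterion.

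This is not a complaint that detail has been left to another document. The protocol states the rule, and states it wrongly.

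**Working it through.** The protocol gives no operating figure for this rule, so there is none to reproduce. (Its one derived design figure, 81% power with 44 per group, reproduces at 80.6% by exact enumeration of the two-sided Fisher test and is not in dispute.)

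**Inputs**
- Patients on Peg-IFN: 50 + 50 = 100 (section 3).
- SAE rate per treated patient: p = 0.06 (section 6.2). Using it here is an assumption. It could be lower: section 6.2 lists hepatitis B flares among the main SAEs, while section 1 says that low-viral-load patients mostly have inactive disease. Rates of 3%, 2% and 1% are therefore also shown. These three are assumptions with no source in the protocol.
- Drop-out: section 7.5 says "10% drop out is calculated in the power of this study", so 90 patients are shown as a second case. This is cautious, because patients who leave because of side effects may be more likely than others to have had an SAE.

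**Formulas** (binomial, full 48-week exposure, controls and follow-up not counted)
- At least one affected patient: 1 − (1 − p)^n
- At least two: 1 − (1 − p)^n − n·p·(1 − p)^(n−1)

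The second formula covers the reading that the plural in section 7.7 requires more than one.

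**Worked case, p = 0.06, n = 100**
- Expected number affected: 100 × 0.06 = 6
- At least one: 1 − 0.94^100 = 1 − 0.0021 = 0.998
- At least two: 1 − 0.0021 − 6 × 0.94^99 = 1 − 0.0021 − 0.0131 = 0.985

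| Assumed rate | n = 100: ≥1 / ≥2 | n = 90: ≥1 / ≥2 |
|---|---|---|
| 6% | 99.8% / 98.5% | 99.6% / 97.4% |
| 3% | 95% / 81% | 94% / 76% |
| 2% | 87% / 60% | 84% / 54% |
| 1% | 63% / 26% | not computed |

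**How soon.** Section 7.7 is not tied to the interim looks. The smallest n with 1 − 0.94^n ≥ 0.5 is ln 0.5 / ln 0.94 = 11.2, rounded up to 12 fully treated patients. Under the two-patient reading it is 28. At 2% the corresponding numbers are 35 and 84.

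SAEs in the control arm, pregnancies and events in follow-up would only raise these probabilities.

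**The case against.** **The authors meant unacceptable SAEs.** This is the strongest reply. Sections 7.4.1, 8.3.1, 8.3.2 and 11.3 only make sense if the trial goes on after SAEs, so sections 7.7 and 9.2 look like loose shorthand. That stands as a reading of intent. It also stands against a stronger conclusion that a reader might draw from the percentages, namely that the trial would almost certainly be stopped. The percentages are chances that the literal wording is met; the reporting plan shows that stopping at the first SAE was not contemplated. But no text supplies the missing qualifier, and section 9.2 names occurrence itself. Those sections confirm that the written rule does not fit the protocol around it.

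**Section 8.2 contradicts section 7.7, or else rescues it.** A reader might infer either. The documents support neither. Section 8.2 is a statutory duty with its own trigger (harm beyond what was foreseen) and its own consequence (suspension). A stricter termination rule can coexist with it, and nothing makes section 7.7 subject to it.

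**This only asks for a missing threshold.** Thresholds can sit in a SAP or monitoring charter that is not shown, so the absence of a number is no fault in itself. What remains is that the two sentences are worded unconditionally.

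**The rate may be lower here.** It may. At 1% the two-patient reading is met only 26% of the time. The conflict in the text does not depend on the rate.

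**Conclusion.** The point holds as a defect in wording that matters. Sections 7.7 and 9.2 fix an unconditional stopping rule that does not fit the protocol's own expectation of SAEs or its plans for reporting them. If the 6% rate carries over, the rule as written is met with probability 99.8% (at least one affected patient) or 98.5% (at least two) among 100 Peg-IFN patients. At 2% these are 87% and 60%. The figures rest on a binomial count with full 48-week exposure and on the assumed rate.

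The consequence is that the trial either stops on foreseen events or departs from its own rule at each one. No effect on the endpoint, the significance level, the power or the data collected has been shown. It should be corrected by amendment.

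**What to change.** **Section 7.7.** Replace the sentence with wording such as: *The study is suspended for METC review as in section 8.2 if the nature, severity or frequency of SAEs suggests harm to participants significantly beyond what was foreseen (reference: the kinds of SAE and the 6% rate in section 6.2). It is terminated if that review so concludes.*

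**Section 9.2.** Refer to the rule in section 7.7 in place of the occurrence of SAEs.

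**Numeric boundary: optional.** If one is used, it should supplement this trigger and not replace it. As an illustration, 11 or more affected of 100 Peg-IFN patients is reached with probability 3.8% at a true rate of 6% and 67% at 12%. If the background is really 2% or 3%, the same boundary detects a doubling (to 4% or 6%) only 0.2% or 3.8% of the time. A single cumulative count is also slow to react to an early cluster, and it gives no special weight to deaths. Someone would have to be named to set and watch it: a data safety monitoring board appears only in the abbreviation list.

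**Cost.** Two sentences by amendment, with no change to sample size, visits or data collection. The downside is that the new trigger needs judgement and is less automatic than the present wording.
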